### 330 In-Kind Funding

- 331 - **The Indian Health Service** – The IHS will fund all patient scales, allow for lab work to occur at IHS
- 332 facilities free of charge, and provide funding for patient navigators and heart failure nurses to
- 333 assist in tracking patients, calling patients to remind them of lab work, assisting with completion
- 334 of patient-reported outcomes/surveys and case report forms for trial outcomes. They will also
- 335 provide a freezer at Tohatchi Health Clinic (to serve as a mini-hub for Northern catchment area).
- 336 - **[name]** with funding through the **Robert A. Winn Diversity in Clinical Trial Career**
- 337 **Development Award** will fund clinical trial support through the clinical research collaboration
- 338 unit at Penn.
- 339 - **Tocabe Inc-** will donate recipe cards of the meals provided, as well as the recipe cards for the
- 340 control group.
- 341 - **The Gallup Food Pantry-** will donate their freezer space and have agreed to serve as the central
- 342 food hub to meal delivery and will provide their services for decentralized patient meal delivery
- 343 including their mobile delivery unit as needed.
- 344

### 345 Additional Stakeholders and Partners

- **Navajo Area Department of Health-** [name], who serves as the Director for the Navajo Area Department of Health for the IHS, is fully supportive of this study and will serve on our community advisory board. She works closely with the Navajo Nation Department of Health, who are also supportive of this work. We will be working closely with the Navajo Nation Department of Health on this study so that if our program is effective, we can leverage our partnerships with tribal leaders to secure pathways to allow for sustainable funding and adoption of this program long-term.
- **Indian Health Service Headquarters Office of Quality:** Our team includes [name], improvement advisor, and [name], director of quality improvement for the IHS HQ Office of Quality Division of Innovation. This study is supported by an Indian Health Service Innovations Award, which provides logistical support from the IHS Office of Quality. Additionally, as part of an IHS innovations award, the results of this study may inform adoption and expansion more broadly throughout the IHS of such programs.
- **Indian Health Service Headquarters Food is Medicine Coalition:** Our community advisory board includes [name] who is the principal nutrition consult for the IHS nationally and serves as the IHS representative for the federal agencies' Food is Medicine Coalition. These results will be critical to allow the coalition to advocate for increased congressional funding to support food is medicine initiatives throughout the HIS nationally.
- **Shiprock Farmers Coalition/Local Navajo Farmers:** To locally source ingredients for our meals with Tocabe, we will be partnering with local farmers coalitions such as the Shiprock Farmers Coalition and other local produce and livestock farmers to support local economic development and support local food systems.

## Study Timeline

|                                                           | YEAR 1 |    |    |    |    |    |    |    |    |     |     |     | YEAR 2 |     |     |     |     |     |     |     |     |     |     |     |
|-----------------------------------------------------------|--------|----|----|----|----|----|----|----|----|-----|-----|-----|--------|-----|-----|-----|-----|-----|-----|-----|-----|-----|-----|-----|
|                                                           | M1     | M2 | M3 | M4 | M5 | M6 | M7 | M8 | M9 | M10 | M11 | M12 | M13    | M14 | M15 | M16 | M17 | M18 | M19 | M20 | M21 | M22 | M23 | M24 |
| Phase I: Meal Curation of Traditional Navajo Meals        | X      | X  | X  |    |    |    |    |    |    |     |     |     |        |     |     |     |     |     |     |     |     |     |     |     |
| Phase I: Secure supply chain                              | X      | X  | X  |    |    |    |    |    |    |     |     |     |        |     |     |     |     |     |     |     |     |     |     |     |
| Phase I: Secure local suppliers for produce and livestock |        | X  | X  | X  |    |    |    |    |    |     |     |     |        |     |     |     |     |     |     |     |     |     |     |     |
| Eastern Navajo Agency Council Approval                    |        |    | X  | X  | X  |    |    |    |    |     |     |     |        |     |     |     |     |     |     |     |     |     |     |     |
| IRB Approval                                              |        |    |    | X  | X  |    |    |    |    |     |     |     |        |     |     |     |     |     |     |     |     |     |     |     |
| Phase I: Pilot feasibility (n=20)                         |        |    |    |    | X  | X  |    |    |    |     |     |     |        |     |     |     |     |     |     |     |     |     |     |     |
| Phase I: Pilot feasibility outcome assessment             |        |    |    |    |    | X  | X  |    |    |     |     |     |        |     |     |     |     |     |     |     |     |     |     |     |
| Phase II: Trial                                           |        |    |    |    |    |    |    |    |    |     |     |     |        |     |     |     |     |     |     |     |     |     |     |     |
| Determine eligible sample in our healthsystem             |        | X  | X  | X  | X  | X  | X  |    |    |     |     |     |        |     |     |     |     |     |     |     |     |     |     |     |
| Enrollment                                                |        |    |    |    |    |    |    | X  | X  |     |     |     |        |     |     |     |     |     |     |     |     |     |     |     |
| 25% Sample Size (n=50)                                    |        |    |    |    |    |    |    |    | X  | X   |     |     |        |     |     |     |     |     |     |     |     |     |     |     |
| 50% Sample Size (n=100)                                   |        |    |    |    |    |    |    |    |    | X   | X   |     |        |     |     |     |     |     |     |     |     |     |     |     |
| 75% Sample Size (n=150)                                   |        |    |    |    |    |    |    |    |    |     | X   | X   |        |     |     |     |     |     |     |     |     |     |     |     |
| 100% Sample Size (n=200)                                  |        |    |    |    |    |    |    |    |    |     |     | X   | X      |     |     |     |     |     |     |     |     |     |     |     |
| Study Period-Primary Outcome                              |        |    |    |    |    |    |    |    |    |     |     |     |        |     |     | X   |     |     |     |     |     |     |     |     |
| Study Period-ALL Outcome Assessments Ends                 |        |    |    |    |    |    |    |    |    |     |     |     |        |     |     |     |     |     | X   |     |     |     |     |     |
| Data Analyses                                             |        |    |    |    |    |    |    |    |    |     |     |     |        |     |     |     |     |     | X   | X   | X   |     |     |     |
| Present to Stakeholders and Tribal Council                |        |    |    |    |    |    |    |    |    |     |     |     |        |     |     |     |     |     |     |     | X   | X   | X   |     |
| Dissemination                                             |        |    |    |    |    |    |    |    |    |     |     |     |        |     |     |     |     |     |     |     |     | X   | X   | X   |

## Protection of Human Subjects: Protection of Human Subjects:

This study is aimed at implementing a model to improve access to healthy, nutritious foods for patients. Therefore, this poses a minimal risk to patients. There is prior literature that suggests that medically tailored meal delivery improves quality of life, including Kansas City Cardiomyopathy Questionnaire summary score, as well as potentially a trend to lower heart failure hospitalizations, without significant diet-related adverse events.[4]

However, there are no prior studies of medically and culturally tailored meals in this population. However, our pilot feasibility trial has demonstrated no safety concerns and we will be medically tailoring meals to meet guideline recommendations.[6][7] Meals will be designed with registered dietician input to ensure safety is optimized. Given the short duration of the intervention and low-risk of the intervention, we will not perform interim safety analyses.

Human subjects' involvement, characteristics, and design: The studies outlined in this proposal depend on the enrollment of individuals with heart failure. No vulnerable populations are being specifically

targeted. We are limiting enrollment to individuals above age 18 years as the etiology and practices surrounding heart failure in pediatrics populations differ significantly from those in adults. All data is transmitted in encrypted and secure fashion, stored on servers with "triple-lock" certification, and is available only to members of the study team, IRB, and any state or federal agencies with auditing power.

Sources of Materials: No biological materials will be obtained or stored as part of these studies. Only data, as collected during set time points from the EHR will be obtained. Data includes medical record elements such as demographics, pharmacy records such as medication prescription and dosing, laboratory values, and administrative codes. All data will be stored without PHI. However, we will retain a linking dataset to be able to re-link individual data to actual patients for future studies and ongoing efforts through the HIS. Access to individually identifiable information will be limited to the PI of the study, and only then via a linking file as aforementioned. All data used for analysis and dissemination to other investigators will be de-identified.

Over or under treatment: Providers will be blinded to patient treatment assignment and thus it is unlikely that treatment will differ between patients. However, we will also be extracting medication changes during the study period to ensure there were no significant differences in medical therapy treatment between the two groups.

Potential benefits of the proposed research to the subjects and others: Subjects in this study may directly benefit from receiving healthier food options for their care. In addition, this may improve their knowledge on healthy and traditional foods and dietary practices that may be sustained after the duration of the study. Additionally, the results of these studies may lead to significant benefit in the IHS and other rural Indigenous communities. This model could be similarly expanded to other sites. The risk/benefit ratio, given the minimal risk to study subjects, is more than acceptable in this series of studies.

#### **Data and Safety Monitoring Plan:**

- What is the investigator's assessment of the overall risk level for subjects participating in this study?

We believe that this poses minimal risk to the patients.

- If children are involved, what is the investigator's assessment of the overall risk level for the children participating in this study? No children will be involved.

This study poses **i. Minimal risk** ii. Greater than minimal

The principal investigators (PI) is responsible for monitoring the data, assuring protocol compliance, and conducting the safety reviews at the specified frequency regularly. During the review process the PIs will evaluate whether the study should continue unchanged, require modification/amendment, or close to enrollment. The PIs or the Navajo Nation Human Research Review Board (Navajo Nation IRB) have the authority to stop or suspend the study or require modifications.

This protocol presents minimal risks to the subjects and Unanticipated Problems Involving Risks to Subjects or Others (UPIRSOs), including adverse events, are not anticipated. In the unlikely event that

such events occur, Reportable Events (which are events that are serious or life-threatening and unanticipated (or anticipated but occurring with a greater frequency than expected) and possibly, probably, or definitely related) or Unanticipated Problems Involving Risks to Subjects or Others that may require a temporary or permanent interruption of study activities will be reported immediately (if possible), followed by a written report within 5 calendar days of the Principal Investigator becoming aware of the event to the IRB (using the appropriate forms from the website) and any appropriate funding and regulatory agencies. The investigator will apprise fellow investigators and study personnel of all UPIRSOs and adverse events that occur during the conduct of this research project through regular study meetings and via email as they are reviewed by the principal investigator.

#### **Statistical Considerations**

Sample Size Determination: The primary outcome is the rate of hospitalization or ER visits within 90 days post randomization. Our preliminary data suggests that the hospitalization rate and ER visit for 90 days is approximately 29%, and based on prior data, we hypothesize a reduction to 13% [4]. We will therefore need a sample size of 204 patients to detect a statistically significant difference with 80% power and an alpha error rate of 0.05.

Interim Analysis: Given no safety concerns during our pilot trial, the short duration of the intervention, and low-risk of the intervention, we will not perform interim safety analyses.

#### Statistical Analysis:

The primary analysis will use the intention-to-treat principle. Between-group differences in baseline characteristics will be assessed using  $\chi^2$  tests for dichotomous variables and 2-sample t tests for continuous variables. Within-group randomization to week 8 changes in continuous outcomes including laboratory evaluation and biomarkers, CCS, and KCCQ score, will be evaluated using paired t-test.

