**Research Plan:** We plan to conduct a randomized, comparative effectiveness design trial, with 1:1 randomization. This will be done at two IHS clinical sites in the Gallup Service Unit at Indian Health Service: Gallup Indian Medical Center (GIMC) and Tohatchi Health Clinic (THC), with the plan to expand to Fort Defiance Medical Center and/or Shiprock Medical Center if we are unable to enroll our target sample size.

**Study Population:** All patients 18 years of age or older, with diagnosis of heart failure based on ICD code I50\* with a hospitalization (any cause) in the last 12 months. Only patients with active prescription through IHS and engaged in care at our centers (clinical visit within last 12 months) will be included. We will exclude patients on hospice care or those residing in an acute care or skilled nursing facility, or any patient currently residing outside of the 50-mile IHS Gallup Service Unit catchment area.

**Subject Recruitment:** Eligible patients are identified through a query through iCARE, a EHR based data system through the IHS EHR. Patients with ICD10 diagnostic criteria for HF will be identified (ICD10\*). The inclusion criteria will be all adults  $\geq 18$  years, who have a prescription in the IHS system in the last 12 months and have had a clinical visit at GIMC or THC in the last 12 months, as well as a hospitalization (all-cause) in the last 12 months. Patients will be consented verbally either at the health center or verbally over the phone to enroll. If we have not met our 50% enrollment goal by 6 months, we will expand enrollment to another Navajo IHS site—Fort Defiance and/or Shiprock Medical Center, and enroll patients with ER visit (rather than just hospitalization) in the last 12 months.

**Enrollment:** All patients that meet eligibility criteria and consent to participate will be enrolled to receive meal delivery simultaneously: all enrolled patients will start receiving the intervention at the same starting time point,  $t=0$ . Patients randomized to usual care will also start the “intervention” of usual care at the time  $t=0$ , so that all patients will have outcome assessment on the same time schedule. For operation and logistical considerations, all baseline assessment (including consent, enrollment, baseline surveys and lab work) will occur in the enrollment period (-45 to 0 days prior to the intervention period). No clinical events will be included during the enrollment period as an outcome.

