|                                                 | X                                                                                                                                                | X                    |                      | X                                                                                                                                                | X           |
|                                                 | Blood Pressure                                                                                                                                   |                      |                      | Blood Pressure                                                                                                                                   |             |
|                                                 | Weight                                                                                                                                           | Weight               |                      | Weight                                                                                                                                           | Weight      |
| Primary Outcome: ER visits and hospitalizations |                                                                                                                                                  |                      |                      |                                                                                                                                                  |             |
|                                                 | X                                                                                                                                                | X                    |                      | X                                                                                                                                                | X (90 days) |
| Food Survey                                     |                                                                                                                                                  |                      |                      |                                                                                                                                                  | X           |

328

329

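### The main analysis text tests baseline characteristics between randomised arms, while the scheduled history of admissions and ER visits has no stated role in the primary comparison

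*Protocol*

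**What the plan says.** The Statistical Analysis paragraph makes three commitments. The primary analysis follows intention to treat. "Between-group differences in baseline characteristics will be assessed using" chi-square tests for dichotomous variables and two-sample t tests for continuous ones. Changes in continuous outcomes to week 8 are examined within each group by paired t test. No test, model or covariate is named for the primary outcome.

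The Data Collection Timeline has a row headed "Primary Outcome: ER visits and hospitalizations", marked at baseline as well as during follow-up. It gives no look-back period and does not say whether a count is recorded. The Study Population paragraph admits patients "with a hospitalization (any cause) in the last 12 months"; the inclusion list also accepts an ER visit. The study team judges eligibility from the medical record. The Enrollment and Enrollment Period paragraphs bar events before day 0 from counting as outcomes.

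Baseline data have other stated uses. Randomisation is stratified by sex, age group and LVEF group. The compliance analysis weights on baseline covariates. Subgroups are defined by EF, gender, age and food insecurity. None of these mentions prior admissions or ER visits.

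**The concern.** A significance test of a baseline difference asks whether chance produced it. With sound randomisation the answer is already known, so the p-value informs no decision. It can still mislead in two ways. A small p-value on an unimportant variable tempts the analyst to adjust for it after seeing the data. A large p-value on a strong predictor can be taken as proof of balance when a gap big enough to matter is present.

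Prior hospital and ER use is the same kind of event as the primary outcome, so it is a natural candidate predictor of 90-day use. Patients may enter with one event many months ago or with several recent ones, and the stratification does not balance this. If the history is left out of the primary comparison, the trial may give up some precision and carries any chance imbalance in prior use into its estimate. At stake is some power and some robustness, in a design that has little power to spare.

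**Working it through.** **1. The plan's own figure.** Inputs from Statistical Considerations: event rates "approximately 29%, and based on prior data, we hypothesize a reduction to 13" percent, with "80% power and an alpha error rate of 0.05". Allocation is 1:1. Sidedness is not stated; two-sided is assumed.

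Pooled formula without continuity correction, mean rate (0.29 + 0.13)/2 = 0.21:

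n per arm = [1.960 × √(2 × 0.21 × 0.79) + 0.842 × √(0.29 × 0.71 + 0.13 × 0.87)]² / 0.16²
= [1.960 × 0.576 + 0.842 × 0.565]² / 0.0256 = 100.5, so 101 per arm, 202 in all.

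This is within 1% of the stated 204. Power at 102 per arm is Φ[(0.16 × √102 − 1.129)/0.565] = Φ(0.862) = 80.6%.

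**2. False flags from the baseline tests.** The expected number is 0.05 × k for k variables tested, whether or not they are correlated. The protocol does not fix k. Its lists give 8 survey measures, 11 laboratory parameters, and blood pressure, weight and BMI: 22 before sociodemographic items.

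| Variables tested | Expected false flags |
|---|---|
| 10 | 0.5 |
| 20 | 1.0 |
| 22 | 1.1 |
| 30 | 1.5 |

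The chance of at least one flag at k = 20 would be 1 − 0.95^20 = 64%, but only if the tests were independent, and they are not (weight and BMI, the lipid fractions).

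**3. What such a test can miss.** Assume 40% of patients had two or more prior events. The standard error of the between-arm difference is √(0.4 × 0.6 × 2/102) = 6.9 points, so only gaps above 1.96 × 6.9 = about 13 points are flagged. A gap of 10 points or more arises by chance in about 15% of trials. One of 10 to 13 points would pass as no difference.

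**4. Gain from adjusting for prior use.** Let R² be the share of outcome variance explained by prior use. The documents give no value, so a range is shown. Adjustment acts like a sample of 102/(1 − R²) per arm, put into the power formula of step 1; the last column is 202 × (1 − R²), rounded up.

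| R² (assumed) | Effective n per arm | Power | Total N for 80% power |
|---|---|---|---|
| 0 | 102.0 | 80.6% | 202 |
| 0.02 | 104.1 | 81.4% | 198 |
| 0.05 | 107.4 | 82.6% | 192 |
| 0.10 | 113.3 | 84.5% | 182 |
| 0.15 | 120.0 | 86.5% | 172 |
| 0.20 | 127.5 | 88.5% | 162 |

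**5. Check by simulation.** Prior count was taken as 1 plus a negative binomial with mean 1.5 and size 1, and the outcome as logistic in the log count, calibrated to 29% and 13%. With 1,500 trials per setting, unadjusted power was 80% to 82%. Adjusted power was 81.0%, 83.1%, 85.6% and 87.0% for log-count slopes 0.5, 0.8, 1.1 and 1.4, with a simulation error of about 1 point. At slope 0 there was no loss. A binary high-use covariate (40% prevalence, assumed; 4,000 trials per setting) gave 82.4%, 83.4% and 85.2% for odds ratios 2, 3 and 5, against 81.2% unadjusted.

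**The case against.** The case against has real force on several points.

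- **Covariate choice is usual SAP content, and the SAP is not at hand.** This stands. The protocol never says that the primary comparison is unadjusted. A reader might infer that it is, but the text is silent. The adjustment is therefore a recommendation. The baseline tests are different, because the protocol commits to them and an SAP could drop them only by departing from it.
- **Baseline data are used elsewhere.** This also stands. A reader might infer that the tests are the only between-arm use of baseline data. Stratification, weighting and subgroups show otherwise. What holds is narrower: these are the only between-arm tests named in the main analysis text, and no stated analysis uses prior admissions or ER visits in the primary comparison.
- **The history may not be recorded in usable form.** Partly right. The timeline row gives no look-back and no count, and every patient must have a prior event, so yes/no carries little information. But pre-day-0 events cannot be outcomes, so the baseline mark makes sense only as history, and the records are consulted for eligibility in any case.
- **The gain is assumed and may be nil.** True at the low end of the range.
- **A flagged p-value alone changes neither the primary estimate nor the type I error, and no text says that flagged variables will be adjusted for.** True. The harm is an invitation to data-driven adjustment, not a planned step.

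**Conclusion.** The point holds in this form. The baseline significance tests are stated, serve no purpose under randomisation, and should go. Using prior hospital and ER use in the primary comparison is a sensible, cheap improvement that the protocol does not mention.

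Its size is modest: about 0 to 8 power points above roughly 81% at 102 per arm, for assumed R² from 0 to 0.20. It depends on how well the 12-month count predicts 90-day events, which the documents do not report, and on the count varying between patients. The expected number of false flags, about one per 20 variables tested, depends only on how many are tested.

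A reader might go on to infer that the trial is underpowered without adjustment or that 204 is wrong. Neither follows: 204 reproduces, and it gives the planned power unadjusted under the stated rates.

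**What to change.** 1. In Statistical Analysis, replace the chi-square and t tests of baseline characteristics with descriptive summaries by arm.
2. State in advance, whatever balance is observed, that the primary between-arm comparison of the 90-day proportion is adjusted for the count of hospitalizations plus ER visits in the 12 months before enrollment (for example logged), together with sex, age group and LVEF group. One suitable form is a logistic model reported as a standardised risk difference, with the unadjusted proportions in support.
3. In the Data Collection Timeline, define the baseline entry as that count and give its 12-month look-back.

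The cost is a wording change, extraction of a count from records already consulted for eligibility, and a slightly more complex primary model. No extra patients or visits are needed.

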We, therefore, in discussion with community members and tribal partners at two Indian Health Service (IHS) sites in Navajo Nation, will implement and evaluate the effectiveness of a medically and Native-sourced culturally tailored meal delivery program to improve outcomes in heart failure in rural Navajo Nation. This study includes two phases, with a phase I pilot feasibility study, followed by phase II—a comparative effectiveness randomized controlled trial to compare the implementation of our medically and culturally tailored meal delivery program compared to usual care. Phase I outcomes included implementation outcomes such as feasibility and acceptability to inform phase II. The primary outcome for the trial in Phase II will be the proportion of patients who have a hospitalization or ER visit for any cause within 90 days post implementation period start date. Secondary outcomes will include: heart failure hospitalizations specifically, ER visits for volume overload specifically (ER visits for lower extremity edema, dyspnea, with clinical evaluation consistent with volume overload) within 90 days, Kansas City Cardiomyopathy Questionnaire clinical summary score at baseline and at 60 days; prescription adherence rates (% of filled prescriptions out of prescriptions made) for all medication as well as GDMT specifically at 60 days, weight at baseline (and BMI) at 60 days, and the following lab parameters and biomarkers at baseline and at 60 days: albumin, prealbumin, creatinine, NT-proBNP,

HbA1c, total cholesterol, LDL-C, HDL-C, Triglycerides, CRP, urine albumin:creatinine ratio. We will also collect measures of and measures of food insecurity, financial stress, Indigenous cultural connectiveness using the validated Cultural Connectedness Scale-California (CCS-CA), the Indigenous Nourishment Scale, as well as qualitative analyses of patients and local food suppliers to evaluate how this program strengthens local food systems. We will also evaluate food diaries and perform a survey at 90 days to evaluate for any sustainable change in diet and behavior post intervention. Semi-structured interviews will be performed of stakeholders including a subset of patients, primary care providers and food suppliers to assess implementation outcomes.

**Probable Duration of Project:** 24 months

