#### 3. Multiple Imputation for Missing Compliance Data:

- Missing adherence data will be handled using multiple imputation techniques to minimize bias and maintain analytical power.

Subgroup: We perform subgroup analysis based on EF (LVEF <50, and >50%), gender, age (<65 and ≥65 years), and food insecurity (those with low or very low food security vs. food secure). We will also analyze for significant changes in weight in those with obesity (BMI ≥ 30mg/kg), HbA1c among those with diabetes (HbA1c ≥ 7), and cholesterol (total, triglycerides and LDL) among those with baseline hyperlipidemia.

Semi structured interviews will be audio-recorded and transcribed for thematic analysis. Transcripts will be analyzed using an integrated approach, an iterative process to determine themes and patterns present in the data.[18] The interviewers will develop the initial codebook together, and then will independently dual code subsets of the transcripts to identify common themes and iteratively develop a final codebook, with periodic assessment of inter-rater reliability. We will follow the consolidated criteria for reporting qualitative research (COREQ) guidelines.[19]

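### The only analysis stated for the continuous secondary outcomes is a within-arm paired t-test, which does not estimate the effect of meals versus usual care

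*Protocol*

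**What the plan says.** The protocol's Statement of Purpose describes Phase II as "a comparative effectiveness randomized controlled trial to compare the implementation of our medically and culturally tailored meal delivery program compared to usual care", and the Research Plan adds: "We plan to conduct a randomized, comparative effectiveness design trial, with 1:1 randomization". The Endpoints paragraph lists the KCCQ and eleven laboratory measures, at baseline and 60 days, as secondary outcomes of that trial. Cultural connectedness (CCS) follows as a further secondary outcome on the same schedule.

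The Statistical Analysis section has three sentences.
- The first sets the principle: "The primary analysis will use the intention-to-treat principle".
- The second, which begins "Between-group differences in baseline characteristics will be assessed using", assigns chi-square and two-sample t tests to baseline characteristics.
- The third covers the continuous outcomes: "Within-group randomization to week 8 changes in continuous outcomes including laboratory evaluation and biomarkers, CCS, and KCCQ score, will be evaluated using paired t-test".

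The Subgroup paragraph adds: "We will also analyze for significant changes in weight in those with obesity". It defines obesity by BMI of at least 30, and it plans the same kind of analysis for HbA1c in patients with HbA1c of at least 7 and for lipids in patients with hyperlipidemia at baseline. It names no test and does not say whether the changes are within or between arms.

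**The concern.** The named tests do not fit the design. Between-arm tests are assigned to baseline characteristics, where randomisation already makes any difference a matter of chance. The outcomes that need the randomised contrast get a before-and-after test inside each arm. That test cannot separate the effect of meals from change that both arms share.

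The protocol itself makes shared change plausible. All patients receive a scale and a blood pressure cuff. Usual-care patients receive recipes and an educational booklet. Patients know their assignment, so patient-reported scores can shift in either arm.

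Finding significance in the meal arm and none in usual care is not a test of the difference between them. If these analyses were the basis for the secondary conclusions, changes in KCCQ, biomarkers and CCS could be credited to the meals with no treatment effect present. The subsets in the Subgroup paragraph add a second route. Patients selected for a high baseline value tend to have a lower value later, with or without treatment.

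**Working it through.** **Sample size, for the number per arm.** Inputs from Statistical Considerations: 29% versus 13%, 80% power, alpha 0.05. Sidedness is not stated; two-sided is assumed. With pooled variance and mean proportion 0.21:

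n = [1.960 × √(2 × 0.21 × 0.79) + 0.842 × √(0.29 × 0.71 + 0.13 × 0.87)]² / 0.16² = 100.5, so 101 per arm and 202 in total.

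This is within two patients of the stated 204, so 102 per arm is used below. The figure does not decide the point, which concerns the method of analysis.

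**Within-arm test with no treatment effect.** Assumptions: 102 patients per arm with complete data, independent patients, and the same true mean change d (in SDs of change) in both arms. The documents give neither d nor an SD, so a range is shown. The paired t statistic has 101 degrees of freedom and noncentrality d√102 = 10.1d. Let p be the chance of a significant improvement in one arm. The chance of significance with meals but not with usual care is p(1 − p).

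| Shared change d | Noncentrality | p (meal arm significant) | p(1 − p) (meals only) |
|---|---|---|---|
| 0 | 0 | 0.025 | 0.024 |
| 0.1 | 1.01 | 0.169 | 0.140 |
| 0.2 | 2.02 | 0.516 | 0.250 |
| 0.3 | 3.03 | 0.851 | 0.127 |
| 0.4 | 4.04 | 0.979 | 0.02 |

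A between-arm test of change, or ANCOVA, removes the shared change. Its error rate in favour of meals is 2.5% in every row.

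**What each test can detect.** With 80% power and 102 per arm:
- the between-arm comparison detects (1.960 + 0.842) × √(2/102) = 0.39 SD of change;
- the paired test detects (1.960 + 0.842)/√102 = 0.28 SD.

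The paired test looks more sensitive only because it measures total change, not a treatment effect.

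**Subsets chosen on a high baseline.** If patients are selected above +0.5 SD on a normally distributed measure, their mean baseline is φ(0.5)/(1 − Φ(0.5)) = 1.141 SD. With test-retest correlation ρ, the expected fall without treatment is (1 − ρ) × 1.141:
- ρ = 0.98: 0.02 SD
- ρ = 0.9: 0.11 SD
- ρ = 0.8: 0.23 SD

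Both the cut and the correlations are assumptions. The fall biases a within-arm analysis. In a between-arm analysis it cancels in expectation.

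**The case against.** The strongest reply is that the Statistical Analysis section is plainly not exhaustive. It names no test for the primary outcome either, yet the sample size shows that outcome is to be compared between arms. The per-protocol section plans a comparison with usual care and sets the results beside the intention-to-treat effect size, which implies that a between-arm estimate exists. A statistical analysis plan, not shown here, may supply the model.

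Part of this stands. A reader might infer that the secondary outcomes will never be compared between arms, and that every continuous secondary conclusion will therefore be invalid. The document does not say so. It does not forbid a between-arm test or call the paired test the sole inference. But the protocol is not silent on these outcomes: it assigns them a method, and that method does not answer the trial's question. The per-protocol passage does not repair this, because it names no test and concerns a cohort selected on adherence.

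A reader might also infer that spurious benefits are certain. They are not: the inflation needs a shared change that the documents do not quantify. Recovery after the qualifying event is a weak reason to expect one, because that event may be of any cause and up to 12 months old. Nor is 25% a typical figure. It is the largest value that p(1 − p) can take, and the meals-only chance is lower on either side of 0.2 SD.

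For the subsets, the text does not say the analysis is within arm. Hyperlipidemia has no stated cut-off and may be a diagnosis, so the regression argument applies to BMI and HbA1c only. For weight, where the correlation over 60 days may be very high, the effect could be negligible.

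**Conclusion.** The point holds in this form: the only method the protocol states for its continuous secondary outcomes does not estimate meals versus usual care, and it can show a spurious benefit. How often depends on the assumed shared change. Over 0.1 to 0.4 SD, a significant meal-arm result with no treatment effect ranges from about 17% to 98%, and the meals-only pattern from about 2% to 25%, against 2.5% for a valid test. These figures assume 102 complete, independent patients per arm. Regression to the mean in the BMI and HbA1c subsets is a risk only if those analyses are done within arm, and its size turns on the test-retest correlation. The primary outcome and the sample size are untouched. This should be fixed before outcome data are analysed, but it does not threaten the trial's main result.

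**What to change.** Replace the paired t-test sentence with wording such as: Day-60 continuous outcomes will be compared between arms by intention to treat, using ANCOVA on the day-60 value adjusted for the baseline value, sex, age group and LVEF group, with standard errors that allow for patients of one household sharing an assignment; the adjusted mean difference will be reported with its 95% confidence interval. Skewed markers will be log-transformed as needed. Within-arm changes are descriptive only.

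State that the obesity, diabetes and hyperlipidemia subsets use the same between-arm model. The household provision is needed because the Randomization section gives members of one household the same assignment.

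A two-sample comparison of change scores, with the same household allowance, would also cure the defect. ANCOVA is preferred for precision: at an assumed baseline-to-follow-up correlation of 0.6, its variance is (1 + 0.6)/2 = 0.80 of that for change scores.

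The cost is wording and a little analysis work. The Endpoints section already schedules the measures at baseline and 60 days, so no new data or patients are needed.
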